## 22 Allocation concealment, randomization and blinding procedures

### 23 Allocation concealment and randomization

Following informed consent, subjects will be assigned a unique subject identification number (section 3.2.2) and details recorded on an enrollment log. If eligibility is confirmed according to the defined inclusion and exclusion criteria (section 5.3), children will be randomized into one of the three equally sized groups as defined in section 3.1 above (for groups A, B and C).

Randomization will be undertaken using pre-prepared, sealed opaque envelopes to maintain allocation concealment. Block randomization stratified by sex will be undertaken using a computer generated randomization sequence pre-prepared by an individual not otherwise involved in the study or its analysis. The block size and randomization sequence will not be known by any member of the investigator team, hence ensuring allocation bias is avoided. Information regarding the group into which a participant has been randomized will be revealed to the team only when opening the envelope.

At the time of randomization, the person undertaking randomization will take the next envelope in numerical sequence. The randomization list will be cross-checked by a second individual both of whom will be required to sign to document the process.

The 35 subjects for group D will be recruited sequentially after recruitment in groups A, B and C have been completed, during the 2nd recruitment season (January – June 2018).

## 24 Participant identification

Once informed consent is provided, subjects will be allocated a unique subject identification number (and recorded on the screening log). The number will consist of the letters 'NAS' followed by 3 digits (e.g. NAS001). If eligibility is confirmed and the subject randomized, a suffix relating to the randomized group will be added to the identification number (e.g. NAS001A, NAS001B, NAS001C, NAS001D for groups A, B, C and D respectively). The subjects will subsequently be identified by this number alone on all further study related documentation and laboratory samples. This will facilitate accurate management of the different visit and sampling schedules, as well as laboratory assays, across the different groups.

## 25 Blinding of external laboratories undertaking analyses

Allocation concealment will be maintained as detailed above in section 3.2.1. Laboratory personnel processing samples and performing flow cytometry analyses on blood samples at the MRC Gambia will not be blinded to group allocation as sampling schedules vary across the groups (Tables 1 – 3). Laboratory personnel in external laboratories assessing the nasal and oral IgA, as well as serum HI, immunological endpoints will be blinded to group allocation, as well as whether samples are pre or post vaccine by allocation of a sample number. The code matching these sample numbers, to subject identification number and visit number will be held by investigators at the MRC Gambia.

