#### 16 Exploratory

- (i) To identify novel early systemic and mucosal molecular signatures following LAIV that are associated with subsequent robust serum haemagglutination inhibition (HI) responses.
- (ii) To identify novel early systemic and mucosal molecular signatures following LAIV that are associated with subsequent robust influenza-specific T-cell responses.
- (iii) To describe the association between LAIV virus shedding at day 2 and/or 7 following immunization (as a measure of vaccine ‘take’) and influenza-specific mucosal IgA, serum HI and systemic influenza-specific T-cell responses to LAIV.

- (iv) To explore the impact of antibiotic modulation of microbiota on LAIV-induced nasal gene expression and downstream effects on the mucosal immunogenicity of LAIV.
- (v) To establish whether LAIV increases the burden of *S. aureus* in the nasopharynx.
- (vi) To explore associations between nasopharyngeal microbiome profiles and post-LAIV nasal and systemic gene expression profile changes.
- (vii) To explore whether the presence of respiratory viruses in the nasopharynx at the time of LAIV administration impacts on influenza-specific mucosal IgA, serum HI and systemic influenza-specific T-cell responses to LAIV
- (viii) To establish whether an expansion in peripheral T-follicular helper (pTfh) cells occurs following LAIV.
- (ix) To explore whether early systemic monocyte expansion following LAIV is associated with subsequent robust mucosal IgA responses.
- (x) To explore whether an expansion of IgA-expressing B-cells with a mucosal-homing phenotype is detectable in blood following LAIV and whether this expansion correlates with the subsequent nasal and oral influenza-specific IgA response.
- (xi) To explore how interferon-induced transmembrane protein-3 (IFITM3) host gene polymorphisms may impact on early innate and later influenza-specific immune responses induced by LAIV.
- (xii) To explore the correlation between systemic HI and oral fluid immunoglobulin G (IgG) responses, to assess the suitability of the latter as a proxy measure of LAIV-mediated seroconversion obtained via non-invasive means.

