## 20 Study design

### 21 Type of study and design

All primary objectives and most exploratory objectives will be addressed through the conduct of a phase 4, randomized, controlled clinical vaccine trial. A total of 330 healthy children aged 24 – 59 months will be enrolled into one of three groups of equal size (3 x 110 children):

- (i) LAIV-vaccinated (Group A - blood sample at day 0, 2, 21)
- (ii) LAIV-vaccinated (Group B - blood sample at day 0, 7, 21)
- (iii) Control group (Group C)

Allocation concealment will be maintained from the start through the use of sealed envelopes. Block randomization stratified by sex will be used and a randomization sequence will be generated by an MRC Statistician not involved in the study. Investigators will not be blinded to group allocation from this point onwards as the sampling schedule differs between groups. Local laboratory staff will therefore not be blinded for this reason, but samples sent to external laboratories will be blinded (see section 3.2.3).

Two LAIV-vaccinated groups are included in order to achieve several exploratory objectives, which require blood sampling at different time points following vaccination, whilst minimizing the number of times children are bled times (i.e. 2nd blood sample at either day 3 or day 7 post-LAIV, but not both). The unvaccinated subjects will serve as a control group for the primary objective of assessing the impact of LAIV on the nasopharyngeal microbiome. Section 8 details the statistical considerations made to decide on the sample sizes to be recruited. The vaccination and sampling schedules for groups A, B and C are detailed in Tables 1.

Group C subjects will be administered LAIV after the NPS is taken on their day 21 visit, to offer them the same level of protection against influenza illness by participating in the study as those in groups A, B and D.

An additional 35 healthy children aged 24 – 59 months will be recruited in the 2nd phase of recruitment (Jan – June 2018) to assess the objective of how modulation of the nasopharyngeal microbiome with antibiotics impacts the mucosal immunogenicity to LAIV

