## **99 Flow cytometry assays**

Fresh whole anti-coagulated blood will be used for optimized exploratory flow cytometry assays at several times points to assess innate cell phenotyping, influenza-specific T-cell responses, B-cell phenotyping and peripheral T-follicular helper cells following LAIV (Table 3). Influenza-specific T-cell responses will be assessed by intra-cellular cytokine staining following stimulation with overlapping peptide sets matching conserved internal proteins (matrix and nucleoprotein) and HA of the influenza A vaccine strains. All these assays will be performed at the MRC Unit The Gambia research immunology laboratory.

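### Unblinded flow cytometry is justified for handling blood but not for gating, and with no unvaccinated child bled, a visit-linked reading shift could not be told from a post-LAIV change

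*Combined protocol and SAP*

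**What the plan says.** Section 21 (Type of study and design) gives the differing sampling schedules as the reason for not blinding investigators, and adds: "Local laboratory staff will therefore not be blinded for this reason, but samples sent to external laboratories will be blinded". Section 25 (Blinding of external laboratories undertaking analyses) applies the same reason to local staff who process samples and to those "performing flow cytometry analyses on blood samples at the MRC Gambia will not be blinded to group allocation as sampling schedules vary across the groups". External laboratories measuring IgA and HI are masked to group, "as well as whether samples are pre or post vaccine by allocation of a sample number". Investigators at the MRC Gambia hold the code.

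Under section 24, once a child is randomized, "a suffix relating to the randomized group will be added to the identification number", and that identifier goes on laboratory samples.

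Section 99 describes the cellular work: "Fresh whole anti-coagulated blood will be used for optimized exploratory flow cytometry assays at several times points". It does not say how populations are gated or by whom. Section 144 leaves laboratory procedures to a laboratory analytical plan that is not among the documents.

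The randomized children enter "one of three groups of equal size (3 x 110 children"). The first is "LAIV-vaccinated (Group A - blood sample at day 0, 2, 21"), and Group B is bled on days 0, 7 and 21. Table 2 has Group D bled on days 0, 2 and 21. For Group C, section 21, Table 1 and the footnote to Table 3 list swabs only.

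Exploratory objective (viii) is: "To establish whether an expansion in peripheral T-follicular helper (pTfh) cells occurs following LAIV". The first half of (x) asks whether an expansion of IgA-expressing B cells can be detected. Objectives (iii) and (ix) and the second half of (x) ask about associations.

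**The concern.** Differing schedules mean that whoever receives a tube will know which group it came from. They do not oblige the person who later sets cell-population boundaries on a recorded file to know. The two tasks can be separated, but section 25 exempts both.

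Cell frequencies depend on where those boundaries are placed. If the reader knows that a file is post-vaccine and places them slightly more generously, the frequency rises with no biological change. In a controlled comparison, a shift common to both arms would cancel. Here every post-baseline blood sample comes from a vaccinated child, so nothing offsets it.

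At stake are the objectives that rest on a within-child change: (viii), the first half of (x), and any comparison of T-cell responses with day 0. A reading artefact there could be reported as a cellular response to the vaccine.

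**Working it through.** **1. Can the files be masked?** Table 3 lists the T-cell, B-cell and pTfh assays at days 0, 7 and 21, and innate profiling at days 0 and 2. Each assay therefore yields comparable files from before and after vaccination. Section 25 already has a sample-number code that hides visit for IgA and HI. Differing schedules do not stand in the way of recoding.

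**2. Is there a bled comparator?** Bled children: 110 (A) + 110 (B) + 35 (D) = 255, all given LAIV at day 0. Bled in Group C: 0.

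**3. Illustration of size.** The plan has no figure to reproduce: it gives no power, SD, cell frequency or gating error for any flow endpoint.

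Inputs:
- n = 110 × 0.9 = 99. Group B size is from section 21; attrition of about 10% is from section 51.
- SD of the within-child log ratio: 0.4, range 0.3 to 0.5 (assumed).
- Same-direction relative shift between visits: 5% or 10% (assumed).
- Paired test of post-vaccine against day 0, two-sided 5%, no true change (assumed).

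Formulas: z = ln(1 + shift) / (SD/√99); false-positive probability = P(Z > 1.96 − z) + P(Z < −1.96 − z).

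At SD 0.4 the standard error is 0.4/9.95 = 0.0402. A 5% shift gives z = 0.0488/0.0402 = 1.21; a 10% shift gives z = 0.0953/0.0402 = 2.37.

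| SD | 5% shift | 10% shift |
|---|---|---|
| 0.3 | 0.366 | 0.885 |
| 0.4 | 0.228 | 0.659 |
| 0.5 | 0.163 | 0.475 |

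**4. The same question without choosing an SD.** Let the shift be d SDs of the within-child difference. The chance of a significant result in the direction of expansion, with no true change, is:

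| d | n = 99 (day 2 or day 7) | n = 198 (A + B, day 21) |
|---|---|---|
| 0 | 2.5% | 2.5% |
| 0.1 | 17% | 29% |
| 0.2 | 51% | 80% |
| 0.3 | 85% | 99% |

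**5. Effect of masking.** In 20,000 simulated trials per setting, the shift was made unrelated to visit, as masked gating intends. The false-expansion rate returned to about 2.5% (about 5% two-sided) for d from 0.1 to 0.3.

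**6. Would a bled control arm do instead?** With 99 bled controls and the same shift in both arms, the two-sided rate is about 5%. If the reader knew the group and shifted only vaccinated children at d = 0.2, false expansions would occur in 29% of trials (99 vaccinated) or 37% (198 vaccinated). A control arm does not replace masking.

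**The case against.** - **Group is not visit.** Section 25 speaks of group allocation. Every bled child is vaccinated at day 0, so knowing A from B does not mark a file as pre- or post-vaccine. This stands as a limit: knowledge of visit is inferred from the visit-specific schedules and from the fact that masking to visit is promised only to the external laboratories.
- **The laboratory plan may deal with it.** The documents do not describe gating, and the laboratory analytical plan may contain safeguards. A reader might infer that staff will be gating files they know to be post-vaccine; the documents do not establish this. But section 25 states a rule rather than leaving a gap, and that plan is to be based on the protocol.
- **No paired test is planned.** Section 129 plans regression of flow outputs against vaccine endpoints. This stands: the test, SD and shifts above are assumptions, and the calculation takes the shift to be in the same direction in every child. Objective (viii) and the first half of (x) still cannot be answered without a pre/post reading.
- **The association objectives are different.** A reader might extend the bias to (iii), (ix) and all of (x). A shift equal in all children largely cancels there. Bias arises only if gating tracks shedding or antibody results. Oral-fluid ELISAs and shedding PCR are also run at the MRC Gambia (sections 97 and 100), but nothing says that gating staff see them.
- **Everything affected is exploratory**, and the externally measured IgA endpoints are masked. This stands and limits the weight of the point.

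**Conclusion.** The concern holds in a limited form. The stated reason supports unblinded processing and acquisition, not unblinded gating, and the protocol already has a way to hide visit. With no unvaccinated comparator bled, a reader-driven shift that follows visit could not be separated from a post-LAIV change in (viii), the first half of (x), or a pre/post T-cell reading.

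The figures of about 23% for a 5% shift and 66% for a 10% shift are not error rates of this trial. They show only that a small consistent shift, if present, would matter at this sample size. The documents do not support a reading that such a shift is likely or that the flow results are invalid.

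This is a worthwhile low-cost improvement to exploratory endpoints. Masking removes reader bias alone: natural change or intercurrent infection between visits would remain.

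**What to change.** Limit the exemption in section 25 to processing and acquisition, and add wording such as:

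> Staff who process and acquire samples are not blinded. Before gating, a person who does not gate recodes the flow files and removes identifiers and acquisition dates. Files are gated by a pre-specified template. Any adjustment for instrument drift is based on run controls and made without knowledge of visit, group, shedding or antibody results. Gating is locked before the code is opened.

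Three details matter. The code is held by investigators at the same site, so the person recoding must be separate from the person gating. Renaming alone may leave dates inside the files. Samples are acquired on different days, so a rigid template without run controls could carry instrument drift into the visit contrast.

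Also state that any expansion will be reported as a within-child change after LAIV, not as LAIV-induced.

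Cost: some file handling, and final gating waits for a child's last sample. No extra visits, blood or assays on participants' samples are needed.

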## 26 Study Vaccine and medication

### 27 Nasovac-S

Nasovac-S is a trivalent live, attenuated influenza vaccine manufactured using the strains recommended by WHO for protection against seasonal influenza. The Nasovac-S to be used in this study will contain the 2016-17 and 2017-2018 WHO recommended northern hemisphere formulations, which consists of three viral strains from influenza A/H1N1, influenza A/H3N2 and an influenza B strain. The 2016-17 Nasovac-S will contain the following strains:

- (i) A/17/California/7/2009/38 (H1N1)
- (ii) A/17/Hong Kong/2014/8296 (H3N2)
- (iii) B/Texas/02/2013-CDC-LV8B

SIIL will update the 2017-18 batch (if a change is required) once the WHO recommendations for that year are released. These strains are (a) **cold-adapted** (i.e., they can replicate at 25°C-33°C, a temperature that is restrictive for replication of many wild-type influenza viruses); (b) **temperature sensitive** (i.e., they cannot replicate at 40°C, a temperature at which many wild-type influenza viruses grow efficiently); and (c) **attenuated** (i.e., they may cause minor symptoms but do not produce classic influenza-like illness). The cumulative effect of the antigenic properties and the cold-adapted, temperature sensitive, and attenuated phenotypes is that the attenuated vaccine viruses replicate in the nasopharynx to induce protective immunity but do not cause influenza like illness or lower respiratory illness.

Within each of the LAIV's three types of reassortant viral strains, six RNA gene segments are derived from a MDV and are responsible for cold adapted, temperature sensitive, and attenuated phenotypes; and two RNA gene segments are derived from the antigenically relevant wild-type viruses recommended by WHO and encode the two surface immunogenic glycoproteins, HA and NA. Thus, the virus contained in Nasovac-S maintains the replication characteristics and phenotypic properties of the MDV and expresses the HA and NA of the current WHO recommended influenza vaccine strains.

## 28 Manufacturer

Nasovac-S is manufactured by the Serum Institute Of India Pvt. Ltd

## 29 Composition

**Table 4. Composition of Reconstituted Nasovac-S:**

| INGREDIENT                   | CONCENTRATION                                    |
|------------------------------|--------------------------------------------------|
| A/California/7/2009 (H1N1)   | Not less than $10^7$ EID 50 /dose     |
| A/Hong Kong/4801/2014 (H3N2) | Not less than $10^7$ EID 50 /dose     |
| B/Brisbane/60/2008           | Not less than $10^{6.5}$ EID 50 /dose |
| Partially hydrolyzed gelatin | 2.5%                                             |
| Sorbitol                     | 5.0%                                             |
| L-Alanine                    | 0.1%                                             |
| L-Histidine                  | 0.21%                                            |
| Tricine                      | 0.3%                                             |
| L-Arginine hydrochloride     | 1.6%                                             |
| Lactalbumin hydrolysate      | 0.35%                                            |
| Phosphate buffer saline      | Base                                             |

Nasovac-S is supplied as a vial containing a freeze-dried cake in a glass vial. Also supplied are an ampoule/vial containing sterile water (for inhalation as diluent), a syringe (for reconstitution), a syringe (for administration), a needle free device, and an intranasal spray device.

## 30 Therapeutic indications

Nasovac-S is indicated in individuals above 2 years of age for the active immunization for the prevention of influenza disease caused by two influenza A subtype viruses and one influenza type B virus expected to circulate in the season of vaccine manufacture.

## 31 Acquisition, storage, transportation and accountability

### 32 Acquisition

The study vaccine will be provided by SIIL and the investigators and their institutions will receive no monetary compensation from SIIL for their participation in this study. The investigator will be personally responsible for vaccine receipt and management or will designate a person who will be responsible for these activities at the MRC Gambia. SIIL will determine with the investigator or the person in charge at the site, the date(s) and time(s) of delivery of vaccine to the MRC Gambia.

The study vaccines will be supplied by SIIL in insulated shipping boxes at 2-8°C. Temperature will be monitored during the shipment. On receipt of the vaccines, the investigator or designee will acknowledge receipt of the vaccines and indicate shipment content, condition, and date. The condition of the packaging on arrival will be assessed and documented according to the applicable unit SOP. The number of vaccines received will be cross-checked with the shipping notification and documented. A reception record will be completed documenting the above and will be filed at the site, as well as being returned to SIIL to confirm receipt.

The investigator shall immediately inform the sponsor (MRC Gambia) and SIIL of any shipment temperature deviation and vaccines quarantined if necessary. The investigators will maintain an inventory/accountability record of study vaccine received. All study vaccines must be accounted for in the accountability record.

SIIL (through the shipping company) will also confirm that the cold chain was maintained during vaccine shipment by confirmation of continuous verification of temperature, freeze watch, and/or cold chain monitoring card. Temperature monitoring will be conducted and verified during transport between the vaccine manufacturer and the site.

### **33 Storage, transportation and handling temperature deviations**

The vaccine will be stored according to vaccine storage requirements at the MRC Gambia, in access restricted refrigerators with a reliable back-up electricity generator and appropriate maintenance records as defined by Unit policy. Storage and transportation of vaccines will be continuously monitored with data logger devices to ensure a continuous temperature record is maintained. Vaccines should be stored and transported at 2-8°C until use. Vaccines will be transported to and from the field site in pre-prepared cold-boxes (e.g. Sofriboxes™) and temperature monitoring throughout the time the vaccines are in the field with the same data logger device. At the field site, the vaccines will be kept in the cool-boxes until reconstituted for administration. Although these will be opened and closed during these procedures, the time the boxes will remain open will be kept to a minimum. As the lyophilized vaccine is stable at standard room temperatures for 2 days, temporary increases in temperature from 2-8°C as boxes are opened and closed is not significant for vaccine stability. The temperature records for all the vaccines transported to and from the site on a given day will be downloaded and filed at the end of each day.

If there is any temperature deviation during transport/storage from SIIL to the study site or from the MRC Gambia to and from the vaccination site, it will be reported immediately to the sponsor according to the temperature monitoring SOP. SIIL state that the lyophilized vaccine is stable for a maximum of 2 days at room temperature. The lyophilized vaccine can also be frozen and is very stable at temperatures below -20 °C. However, the diluent provided should not be frozen. If any vaccine is kept at room temperature for 2 days or more in total (as recorded by the temperature data-loggers) or if the diluent is frozen, the vaccine pack should not be used in the study for vaccinating participants. As some vaccine stock will be used to develop controls for influenza rRT-PCR assays, these stock may still be used for laboratory *in vitro* assays.

